#### Inclusion criteria

2.2.3

The study inclusion criteria are as follows: (1) Meanwhile meet the diagnostic criteria for both asthenospermia and obesity; (2) 22 years old ≤ age ≤ 45 years old; (3) No fertility needs in the past six months; (4) Voluntarily sign the informed consent form.

#### Exclusion criteria

2.2.4

This study exclusion criteria are as follows: (1) Congenital chromosomal abnormalities or microdeletions of the Y chromosome or other known hereditary diseases that may affect semen quality; (2) Combined with oligospermia or obstructive azoospermia; (3) Combined with moderate to severe varicocele cryptorchidism or orchitis or epididymitis or mycoplasma or chlamydia or other diseases that clearly affect semen quality; (4) Combined with diabetes mellitus requiring long-term medication to control blood glucose; (5) Combined with serious cardiovascular diseases or serious cerebrovascular diseases or hematopoietic system diseases or psychiatric diseases or other complications; (6) Receipt of other relevant treatments for this disease such as aromatase inhibitors or estrogen antagonists etc. two weeks prior to treatment; (7) Fear of needles or fainting during acupuncture treatment in the past.

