#### Diagnostic criteria

2.2.2

Diagnostic criteria for asthenospermia and obesity were established in accordance with the World Health Organization Manual for the Examination and Processing of Human Semen (5th Edition) and the “Health Industry Standard of the People’s Republic of China–Measurement of Adult Body Weight” (Standard No. WS/T428-2013) (21, 22). All participants must meet both the diagnostic criteria for asthenospermia and obesity simultaneously.

Diagnostic criteria for asthenospermia: Based on two or more semen analyses, the percentage of progressive motility spermatozoa in the semen is below the reference lower limit of 32%.

Diagnostic criteria for obesity: Based on body mass index (BMI = weight/height^2^), the BMI ≥ 28 kg/m^2^ is defined as obesity.

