#### Termination criteria

2.2.5

The termination criteria are as follows: (1) Participants voluntary withdrawal, such as revoking informed consent; (2) Participants whose condition progressively worsens during the trial, and for whom the physician determines discontinuation of the clinical trial is necessary. To protect the subject, they should withdraw from the trial and receive alternative treatment; (3) Participants develop certain comorbidities, complications, or specific physiological changes rendering continued participation inappropriate during the trial; (4) During the trial, participants demonstrate poor compliance, fails to undergo acupuncture intervention as specified, or uses medications outside the trial protocol that may interfere with trial results (e.g., L-carnitine, aromatase inhibitors, hormonal drugs, etc.); (5) Participants are experiencing serious adverse events; (6) Participants who naturally withdraw or are lost to follow-up during observation, including those who respond to treatment but cannot complete the full course, resulting in incomplete clinical data that may affect efficacy and safety evaluation.

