#### Sample size consideration

2.2.6

This trial employed a randomized, double-blind, parallel-group design. Sample size calculations were based on the primary efficacy indicators, estimated as the change in PR from baseline at week 12 of treatment. Based on our preclinical pilot study, acupuncture treatment for asthenozoospermia yielded a mean percentage change of 6.6 ± 4.2, while sham acupuncture treatment showed a mean change of 3.2 ± 3.7. With α = 0.025 (one-tailed) and β = 0.1 (90% power), the critical value was estimated as δ = 5% (1/5 of the mean change). With a 1:1 trial-to-control ratio, each group requires 30 participants. Strict quality control during the trial will limit the loss to follow-up rate to 20%, resulting in a total study sample of 72 participants, and finally 36 in the trial group and 36 in the control group.

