#### Lifestyle intervention

2.3.1

Both the acupuncture group and the sham acupuncture group will receive health education upon enrollment, including suggestions from the researchers to maintain a regular diet, engage in appropriate exercise (Participants will choose a suitable form of exercise and persist with it; Participants will be recommended a combination of aerobic and resistance training, ensuring each session lasts at least 30 min and is performed at least twice a week), maintain good sleep habits, and avoid prolonged sitting (participants will be advised to get up and move for 10–20 min after every 1–2 h of sitting, with no single sitting session exceeding 2 h; they will also be suggested to sleep before 23:00 pm daily, minimizing or avoiding staying up late).

In addition, participants will be suggested not to take or use any Chinese herbal preparations (such as Shengjing Capsules, Qilin Pills, Compound Xuanju Capsules, etc.), health supplements (such as Vitamin E, Coenzyme Q10), drugs (such as L-carnitine, aromatase inhibitors, hormonal drugs, metformin, liraglutide, semaglutide, etc.), or any other health supplements, weight-loss teas that may affect semen quality or body weight from the researcher’s assessment. Additionally, participants will also be advised to avoid hot water sitz baths, moxibustion, acupoint embedding, and physiotherapy during the study period.

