#### Primary outcome measure

2.4.1

Progressive sperm motility (PR) refers to the proportion of sperm in semen that can move in a straight line or with a larger radius, which is an important indicator for assessing sperm motility. We will assess the PR at week 12 as the primary outcome.

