Although acupuncture is a safe treatment without any pharmaceutical intervention, to avoid delaying participants’ treatment and potential pregnancy plans, we will exclude participants who could intend to conceive within the next six months. During the intervention, participants will decide whether to use contraceptive measures. Pregnancy of the participant’s partner during the intervention period will not affect the continuation of the study. There are currently no published clinical evidence on acupuncture treatment for obese patients with asthenospermia. Our previously studies have indicated that the frequency of acupuncture for treating andrological diseases is typically 2–3 times per week (37, 38), while the treatment course for male infertility with TCM is usually about three months, which aligns closely with the spermatogenesis cycle (39). Therefore, we have set the treatment regimen to three months, with sessions twice a week. In addition, a defining feature of acupuncture is its sustained therapeutic effect, where patients continue to reap benefits long after the whole treatment ends (40). This established phenomenon is precisely why we have designated a 12-week follow-up period.

Our study also has several limitations. First, TCM emphasizes individualized treatment, meaning that the same disease may be treated with different herbal formulas or acupoints. In our study, all participants will receive the same treatment without individualized adjustments. We will conduct further research to determine appropriate acupoint combinations based on the conclusion that acupuncture has efficacy for obese patients with asthenospermia. Second, the practitioners will not be blinded, and acupuncture techniques (including operational proficiency and needle manipulation methods) could not be completely standardized across different practitioners during the implementation. We will provide training for the practitioners before the trial begins, and implement quality control measures to minimize confounding factors. Third, although we standardized the needle insert depth, the sensation of deqi achieved by the participants may vary due to differences in body size. Finally, Single-center recruitment limits generalizability. We will also conduct a multicenter, large-sample randomized controlled trial to further validate the efficacy of acupuncture in treating asthenospermia in obese men in the future.

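### The two-week look-back for prior treatment does not fit the roughly three-month sperm cycle the protocol relies on, so baseline, week 4 and week 8 PR may still reflect earlier therapy

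*Protocol article*

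**What the plan says.** Section 2.2.4 (Exclusion criteria), item (6), excludes men for "Receipt of other relevant treatments for this disease such as aromatase inhibitors or estrogen antagonists etc. two weeks prior to treatment". That is the only look-back for earlier treatment in the article.

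The Discussion explains the length of the regimen: "the treatment course for male infertility with TCM is usually about three months, which aligns closely with the spermatogenesis cycle". It continues: "Therefore, we have set the treatment regimen to three months, with sessions twice a week".

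Two other sections list agents of concern, but only for the study period. Section 2.3.1 (Lifestyle intervention) advises against herbal sperm preparations, supplements and "drugs (such as L-carnitine, aromatase inhibitors, hormonal drugs, metformin, liraglutide, semaglutide, etc", among others, because they may affect semen quality or body weight. Section 2.2.5 (Termination criteria) ends participation for a man who "uses medications outside the trial protocol that may interfere with trial results (e.g., L-carnitine, aromatase inhibitors, hormonal drugs, etc".

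Eligibility on PR is fixed in section 2.2.2: "Based on two or more semen analyses, the percentage of progressive motility spermatozoa in the semen is below the reference lower limit of 32" per cent. Nothing there says how those analyses should be timed relative to earlier therapy. For the outcome, section 2.4.1 says "We will assess the PR at week 12 as the primary outcome", while section 2.2.6 sizes the trial on a quantity "estimated as the change in PR from baseline at week 12 of treatment".

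**The concern.** If about three months are needed for a treatment to show in semen, two weeks off an earlier treatment may not be enough for its effect to have gone. A man who stopped such a treatment just outside the window is eligible, and most of the development of his week 0 sperm took place while he was on it.

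The scope is also narrow. Item (6) covers treatment for the disease, meaning asthenospermia. Every participant is obese (BMI of at least 28), so some may have used a weight-loss drug for obesity alone. The protocol restricts such drugs during the study, but no entry criterion clearly addresses their recent use.

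What is at stake is the meaning of baseline. The change in PR in a recently treated man mixes the response to the trial intervention with the fading of whatever came before. The same applies to the change from baseline in BMI, waist-to-hip ratio and body fat in a man who has just stopped a weight-loss drug. PR at weeks 4 and 8, both named secondary time points, may carry part of the earlier effect as well.

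**Working it through.** **Inputs from the protocol.** Look-back: 2 weeks (2.2.4). Cycle: about three months, taken here as 12 weeks; the Discussion gives it only indirectly. Pilot changes in PR: 6.6 (SD 4.2) for acupuncture and 3.2 (SD 3.7) for sham; one-sided α 0.025, power 90%, 30 evaluable per group (2.2.6).

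**Inputs the protocol does not give, assumed here.** Share of men with recent earlier therapy, f = 10% to 50%. PR points lost as that therapy fades, c = 2 to 6.

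**Step 1: the plan's own figure.** Difference = 6.6 − 3.2 = 3.4. Common SD = √[(4.2² + 3.7²)/2] = √15.665 = 3.96. Then n = 2 × (1.960 + 1.282)² × 15.665 / 3.4² = 28.5, so 29 per group. The t-based version gives 29.5, so 30. The stated 30 is reproduced. Power at 30 per group = Φ[3.4/(3.958 × √(2/30)) − 1.960] = Φ(1.367) = 91%.

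**Step 2: the durations.** The look-back is 2/12 = 17% of the cycle. For a man who stopped just before the window, the largest share of sperm development spent on earlier therapy is max[0, (12 − 2 − visit week)/12]:

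| Visit | Largest share exposed |
|---|---|
| Week 0 | 10/12 |
| Week 4 | 6/12 |
| Week 8 | 2/12 |
| Week 12 | 0 |

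These are upper limits on exposure time, not measurements of carry-over. Week 12 lies at least 12 + 2 = 14 weeks after any treatment that item (6) covers.

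**Step 3: illustration of the change score.** If a share f of men lose c points after baseline, the variance rises by f(1 − f)c², so SD = √[15.665 + f(1 − f)c²]. The table uses the normal approximation, difference 3.4 and 30 per group.

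| f | c | SD | Power | n per group for 90% |
|---|---|---|---|---|
| none | – | 3.96 | 91% | 29 |
| 10% | 2 | 4.00 | 91% | 30 |
| 10% | 6 | 4.35 | 86% | 35 |
| 30% | 4 | 4.36 | 86% | 35 |
| 50% | 2 | 4.08 | 90% | 31 |
| 50% | 6 | 4.97 | 76% | 45 |

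The calculation assumes that the pilot SDs contain no such carry-over and that an unadjusted change score is compared.

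**Step 4: chance imbalance.** The 95% range of the between-group difference due to carry-over alone is ±1.96 × c × √[2f(1 − f)/30], from about ±0.3 (10%, 2 points) to ±1.5 (50%, 6 points). This is the variance of step 3 on another scale, so it is not a further loss.

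**The case against.** The other side has a good deal of substance.

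- **Bias.** A reader might infer that carry-over biases the comparison of acupuncture with sham. It does not: earlier therapy precedes randomization, so its effect is equal between arms in expectation. This stands.
- **The primary time point.** A reader might infer that week 12 PR is contaminated. Step 2 shows it is clear on the protocol's own cycle. Carry-over reaches the primary comparison through baseline, if change is analysed. This stands.
- **The size of the pretreated group.** Inclusion criterion (3) requires no fertility needs in the past six months, which makes recent sperm treatment less likely. The Discussion describes a bar on plans to conceive in the next six months, so how far the criterion helps depends on which is meant. Exclusion (4) removes men with diabetes on long-term glucose medication, and with them many users of metformin and GLP-1 drugs. Item (6) is open-ended, so L-carnitine and herbal sperm preparations can fall under it within its two weeks. All this shrinks the problem but does not lengthen the window or clearly cover drugs taken for weight alone.
- **The reading of the Discussion.** It says that the usual course length matches the sperm cycle, not that an effect on motility lasts a cycle after stopping. The Introduction also describes an action on cation channels in spermatozoa themselves. So carry-over is possible rather than shown.
- **Direction.** The Introduction calls metformin and GLP-1 effects on male reproductive health ambiguous and bariatric effects on semen inconsistent. The documents support no directional claim for these, and recent bariatric surgery is not part of this point.
- **Power.** A reader might infer that the trial is underpowered. Neither f nor c is in the documents, the pilot SDs may already include such men, and the mild case shows almost no loss.

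**Conclusion.** The mismatch is real and internal to the protocol. A two-week look-back does not fit a cycle of about three months, nor the list of agents that sections 2.2.5 and 2.3.1 treat as able to interfere. No other section sets a longer look-back, ties the qualifying semen analyses to a treatment-free period, or clearly covers recent weight-loss drugs.

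The consequence is limited. The between-arm contrast remains unbiased and week 12 PR is largely clear. What suffers is the baseline, the change score on which the trial is sized, the within-arm changes, and PR at weeks 4 and 8. The extra variance is of unknown size; the range of about 91% down to about 76% power rests wholly on assumed inputs and only shows what could happen. Severity is minor to moderate.

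**What to change.** Reconcile sections 2.2.4, 2.2.5, 2.3.1 and the Discussion. The eligibility look-back should be consistent with the cycle used to justify the regimen and should cover the agents the protocol already names as able to affect semen quality or body weight, whether taken for asthenospermia or for obesity. The investigators should set the exact window; none is proposed here.

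Two statistical measures should go with it:

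- Record prior therapy and its stop date for every participant, so that the share of recently treated men is known and can be described by arm.
- Adjust the week 12 comparison for baseline PR. This limits the influence of a distorted baseline, although it cannot by itself identify which men have one.

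The cost is one amended criterion and a little more history-taking at screening. Some men would be deferred or screened out, so recruitment would be somewhat slower. No new trial procedure is needed. Recruitment is planned from November 2025 to October 2026, so the change to eligibility would reach only men not yet enrolled.

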#### Termination criteria

2.2.5

The termination criteria are as follows: (1) Participants voluntary withdrawal, such as revoking informed consent; (2) Participants whose condition progressively worsens during the trial, and for whom the physician determines discontinuation of the clinical trial is necessary. To protect the subject, they should withdraw from the trial and receive alternative treatment; (3) Participants develop certain comorbidities, complications, or specific physiological changes rendering continued participation inappropriate during the trial; (4) During the trial, participants demonstrate poor compliance, fails to undergo acupuncture intervention as specified, or uses medications outside the trial protocol that may interfere with trial results (e.g., L-carnitine, aromatase inhibitors, hormonal drugs, etc.); (5) Participants are experiencing serious adverse events; (6) Participants who naturally withdraw or are lost to follow-up during observation, including those who respond to treatment but cannot complete the full course, resulting in incomplete clinical data that may affect efficacy and safety evaluation.

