#### Blinding

2.2.8

In this study, the acupuncture practitioners will be not blinded, while the participants, outcome data collectors, statistical analysts, and outcome assessors will be blinded. Both the acupuncture group and the sham acupuncture group underwent skin penetration, but the location and depth of the acupuncture will be different. Participants will be in separate rooms, positioned supine for acupoint selection, with curtains drawn below the head to obstruct their view of the specific acupuncture locations. Additionally, appointments will be scheduled for the acupuncture sessions to prevent conversations among the participants.

Participants will be informed prior to randomization: You have a 50% chance of being assigned to either the traditional acupuncture group (deeper needle insertion) or the modern acupuncture group (shallow needle insertion). After the final treatment session at Week 12, each participant will complete a questionnaire asking, “Did you receive traditional acupuncture?” with response options of “Yes,” “No,” or “Uncertain.” Ultimately, Bang’s blinding index and James’s blinding index will be used to assess whether participants could distinguish between receiving real acupuncture or sham acupuncture (23, 24).

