#### Data analysis

2.5.2

Statistical analysis will be performed using SPSS (Chicago, IL, USA). For quantitative data (e.g., PR, sperm concentration, semen volume), normality of distribution will be first assessed. For data meeting normality, descriptive statistics will be presented as mean ± standard deviation. Non-parametric rank-sum tests will be used for non-normally distributed data. Count data will be expressed as frequency and percentage [*n* (%)]. For unordered categorical data, chi-square tests will be applied; for ordered categorical data, non-parametric rank-sum tests will be selected. The test level will be set at α = 0.05. *P* < 0.05 indicated statistically significant differences. For repeated measures data, repeated measures analysis of variance (ANOVA) will be performed. If the sphericity test is not satisfied, the results from the Greenhouse–Geisser correction in one-way ANOVA will be used.

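### The termination criteria do not separate stopping needling from leaving follow-up, so week-12 progressive motility may be selectively missing after randomisation

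*Protocol article*

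**What the plan says.** Section 2.2.5 (Termination criteria) lists six grounds. The fourth applies when "participants demonstrate poor compliance, fails to undergo acupuncture intervention as specified, or uses medications outside the trial protocol that may interfere with trial results". The second covers men whose condition worsens and says that "they should withdraw from the trial and receive alternative treatment". The third covers comorbidities or changes that make further participation unsuitable, and the fifth covers serious adverse events. The first is withdrawal of consent. The sixth is "Participants who naturally withdraw or are lost to follow-up during observation, including those who respond to treatment but cannot complete the full course".

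Section 2.3.1 advises against a long list of herbal products, supplements and drugs, but only as advice: "participants will be suggested not to take or use any Chinese herbal preparations".

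The primary outcome is fixed in section 2.4.1: "We will assess the PR at week 12 as the primary outcome". Table 1 schedules progressive motility (PR) at weeks 0, 4, 8, 12, 18 and 24. On analysis, section 2.5.2 says: "For repeated measures data, repeated measures analysis of variance (ANOVA) will be performed". The article names no analysis population.

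On masking, section 2.2.8 says that "the acupuncture practitioners will be not blinded, while the participants, outcome data collectors, statistical analysts, and outcome assessors will be blinded".

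**The concern.** Two decisions are merged in section 2.2.5. One is clinical: whether a man goes on being needled. The other is about data: whether he is still followed up. The second and third criteria speak of leaving the trial or of no longer participating. The fourth and fifth stand in the same list without a separate meaning. No section says that a terminated man is still asked for his scheduled samples.

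The triggers arise after randomisation and need not be unrelated to outcome. Worsening is directly related to it. Turning to other drugs may follow from a felt lack of benefit. Compliance could also differ by arm, because one arm has deeper needling with manipulation every 10 minutes and the other has insertion of 2–3 mm without deqi.

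If men with poor results leave one arm more than the other, the men left at week 12 are no longer the groups that randomisation made. Losing poor responders from the acupuncture arm flatters acupuncture; losing them from the sham arm works against it.

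**Working it through.** **Inputs from section 2.2.6.** Change in PR 6.6 (SD 4.2) with acupuncture and 3.2 (SD 3.7) with sham; one-sided α 0.025; power 90%; 30 per group, raised to 36 for a 20% loss.

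**The plan's own figure.**
- Difference: 6.6 − 3.2 = 3.4.
- Pooled SD: √[(4.2² + 3.7²)/2] = √15.665 = 3.96.
- n per group = 2 × (1.960 + 1.282)² × 15.665 / 3.4² ≈ 28.5, so 29 by the normal formula. The t-based calculation needs 30 (power 0.905).

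The stated 30 is thus reproduced as a superiority comparison on 3.4 points, and 3.4 is the yardstick for bias below.

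**Bias by formula.** If a share f of one arm is removed, and the removed men differ from the kept men by g SD, the mean of the kept men shifts by f × g × 3.96. The assumptions are f = 0.20 (the planned loss, used only as a convenient size) and a standard error of 3.96 × √(2/28.8) = 1.04.

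| g | Shift, one arm only | Two-sided type I error | Shift, both arms in opposite directions | Two-sided type I error |
|---|---|---|---|---|
| 0 | 0 | 5% | 0 | 5% |
| 0.25 | 0.20 | 5.4% | 0.40 | 6.7% |
| 0.5 | 0.40 | 6.7% | 0.79 | 11.8% |
| 1.0 | 0.79 | 11.8% | 1.58 | 32.9% |

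For example, at g = 0.5 in one arm: 0.20 × 0.5 × 3.96 = 0.40, and 0.40/1.04 = 0.38. The error is then P(Z > 1.96 − 0.38) + P(Z < −1.96 − 0.38) ≈ 0.067.

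**Bias by simulation.** 20,000 trials per setting, no true effect, change with mean 3.2 and SD 3.96 in both arms, 36 per arm, 7 removed per arm (7/36 = 19%), t-test at two-sided 0.05. Removal follows a latent score correlated with the outcome.

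| Correlation, arm 1 / arm 2 | Bias (points) | Type I error |
|---|---|---|
| 0 / 0 | 0 | 5% |
| 0.3 / 0 | 0.40 | 7% |
| 0.5 / 0 | 0.65 | 10% |
| 0.5 / 0.3 | 0.26 | 6.4% |
| 0.3 / 0.3 | 0 | 5.2% |
| 0.5 / 0.5 | 0 | 5.9% |
| 1.0 / 0 (the 7 poorest removed) | 1.3 | 30% |

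As shares of 3.4, 0.40 is 12% and 0.65 is 19%. The last row is a limit, not an expectation. What drives the bias is the difference in selection between arms, not the fact of removal.

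**Cost of keeping the men in.** Suppose a share f of the acupuncture arm stops needling, shows the sham-arm change, and is analysed as randomised, with 36 men measured per group (normal approximation, one-sided 0.025; power is 0.954 at f = 0).
- f = 10%: 3.4 × 0.90 = 3.06, power 0.907.
- f = 16.7%: 3.4 × 0.833 = 2.83, power 0.859.
- f = 20%: 3.4 × 0.80 = 2.72, power 0.830.

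The document gives no non-compliance rate, so these shares are also assumptions.

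**The case against.** The strongest reply is that the article never says terminated men are dropped from the analysis. It names no per-protocol or complete-case set, and analysis sets and missing-data rules commonly stand in an analysis plan that is not shown here. That is right. A reader might infer that the trial is planned as a per-protocol comparison, or that the repeated-measures ANOVA will discard these men. The text does not say so, and its silence on analysis sets is no fault. What remains is a matter of data collection: whether the week-12 sample is taken after termination is settled by the protocol, and an analysis plan can only impute what was not collected.

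A reader might also take the sixth criterion as expelling responders, since it mentions men "including those who respond to treatment but cannot complete the full course, resulting in incomplete clinical data". It does not. It classes as terminated those who have already left or been lost, and deleting it would recover no data.

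Third, practitioners know the allocation, which might suggest that they decide who is non-compliant. Section 2.2.5 does not say who judges compliance. Participants and assessors are blinded, and both arms have skin penetration, the same retention time and the same treatment period. All of this lowers the expected difference between arms. It does not remove it, because worsening and drug-seeking can follow from true differences in response even under perfect blinding.

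Finally, the 20% in section 2.2.6 is planned loss to follow-up, part of which no wording can prevent. This stands, and it is why the figures are scenarios only.

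**Conclusion.** The point holds in a conditional form. Section 2.2.5, chiefly the fourth criterion and also the second, third and fifth, makes post-randomisation events grounds for termination without separating the end of treatment from the end of follow-up. Followed as written, week-12 PR may be missing for reasons linked to outcome and possibly to arm.

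If the selection differs between arms at the moderate strengths assumed (correlation 0.3 to 0.5 in one arm, none in the other, 7 of 36 removed per arm), the bias is about 0.4 to 0.65 points and the type I error about 7% to 10%. If selection is equal, there is no bias and the error stays near 5% to 6%. It cannot be said that the type I error is no longer 5%, only that it may exceed 5%. The document gives no removal rate by arm or by outcome that would decide between these cases. The change is worth making because it is cheap and uncollected samples cannot be recovered later.

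**What to change.** Amend section 2.2.5 as follows, leaving every clinical decision to stop needling unchanged.

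1. Distinguish stopping the intervention from ending study follow-up. Only withdrawal of consent, or actual loss to follow-up, ends data collection.
2. Ask all other men for the week-12 PR sample and the later scheduled assessments, whatever their compliance or other medication.
3. State that the primary outcome is analysed with all randomised men in their assigned group.
4. Record non-compliance and other medication, and use them only in a secondary per-protocol analysis.

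The sixth criterion can stay as a description of men who have left.

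The cost is amendment wording and some effort to follow up men who have stopped needling. No visit is added, since the samples are already in Table 1. Men who stop needling will dilute the estimated effect and lower power, as shown above, and the sponsor should accept this openly. Recruitment is set for November 2025 to October 2026, so the change should be made promptly.
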